### Outcome Measures

The primary outcome assessed will be the changes in participant food insecurity score (evaluated by the HFIS) from baseline to 3 months. Secondary outcomes at 3 months will be changes in dietary habits (evaluated by 2-day 24-hour recall, PREDIMED index [31], and food frequency questions), changes in indicators of nutritional status (body mass index [BMI] and albumin and prealbumin levels), changes in muscle strength improvement (evaluated by dynamometer), changes in quality of life (EQ-5D-3L) [33], changes in fatigue scale (FACIT-F) [34], changes in serological markers of cardiovascular risk (insulin resistance, cholesterol levels, hemoglobin A_1c_, high sensitivity C-reactive protein, adipocytokines, interleukin 1, interleukin 6, and tumor necrosis factor), changes in physical activity (EMS [32] and IPAQ [35]); changes in body composition balance evaluated by bioimpedance, changes in inpatient admissions and outpatient appointments, changes in falls, and changes in knowledge regarding healthy lifestyle.

The secondary outcomes at 6 months will be changes in participant food insecurity score, changes in dietary habits (2-day 24-hour recall, PREDIMED index [31], and food frequency questions), changes in quality of life (EQ-5D-3L) [33], changes in fatigue scale (FACIT-F), changes in physical activity (IPAQ) [35], changes in inpatient admissions and outpatient appointments, changes in falls, and changes in knowledge regarding healthy lifestyle.

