### Sample Size

Sample size was estimated considering a *t* test (independent samples) for comparing the mean change in food insecurity score from baseline to the end of study between group 1 (intervention) and group 2 (control). The intervention is considered to be meaningful if 50% of the individuals in group 1 have a decrease of 1 point in the food insecurity score, all the remaining being unchanged. This results in a difference of –0.5 between the mean changes of the 2 groups. Standard deviation of the change is assumed to be 1.5. Power is set at 0.80 and α=.05. We expect to include and randomize 141 experimental and 141 control elderly people with food insecurity (n=282) equally distributed among the 17 primary care centers. We are prepared to recruit around 70 individuals in each primary care center (a total of 1128 subjects are needed) because we assume that 50% (based on the INFOFAMÍLIA [National Survey on Food Insecurity in Portugal] survey) [36] of the target individuals are food insecure and that 50% of those will adhere to the study.

Of note, the standard approach to sample size calculation based on a clinically important difference was not possible to use in this study because data on interventions in food insecurity are scarce. We have considered the referred effect size based on the INFOFAMÍLIA survey data. In this study, the majority of Portuguese food-insecure households are in low food insecurity level (39.8%), and about 80% of those in the low food insecurity level obtained just 1 point in the food insecurity score, which means that if our intervention decreases the food insecurity score by 1 point we will be able to see a change from the low food insecurity level to the food security level.

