### Randomization, Allocation, and Blinding

Randomization will be computer generated. Randomization will be stratified according to gender and food insecurity level (low/moderate vs severe) with permuted blocks of six. Subjects will be allocated to the study group versus control with a probability of 1:1.

We will ensure researchers taking follow-up outcome measures will be blinded to group allocation; after randomization, the intervention group will be informed that they will have access to the intervention program (TV app) by an independent assessor (single-blind).

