### Data Analysis

Analysis will be performed with Stata software (StataCorp LLC). Continuous variables will be reported as mean and standard deviation (or in case of nonnormal distribution as median and interquartile range). Categorical variables will be displayed as frequencies or proportions. The association between food security status, dietary data, and health outcomes will be assessed through chi-square analysis of baseline data.

To assess the effect of the interventional program on food security, dietary intake, nutritional status and body composition, quality of life, muscle strength, fatigue scale, physical activity habits, and serological markers of cardiovascular risk, 2-tailed *t* tests will be used to compare the amount of change within each group (baseline, end of study [at 3 months] and follow-up [at 6 months]). Independent sample *t* tests will be used to compare the intervention group and control group on the same outcomes.

Dietary intake assessed with 2-day 24-hour recall will be analyzed according to the recommended number of servings from each food group of the Portuguese Food Wheel [37]. Intakes of micronutrients that tend to be low in vulnerable population groups (iron, calcium, folate, and vitamins A, C, and D) will be also analyzed. The percentage of individuals meeting the Estimated Average Requirement or Adequate Intake for iron, calcium, folate, and vitamins A, C, and D will be calculated [38]. Food Processor Nutrition Analysis software (ESHA Research) will be used to estimate the intakes of energy, macro-, and micronutrients.

The association between each outcome and the candidate covariables will be performed using generalized models. We will use multivariate logistic and linear (according to the outcome) regression models. The candidate covariates will be first analyzed by univariate regression. Covariates will enter the multivariate models if their *P* value is less than .25 in univariate analysis or considered clinically relevant in this setting. The selection of covariates will be stepwise by backward selection, according to the level of significance (<.05). Multilevel analysis and sensitive analysis will be performed when appropriate.

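### The planned between-arm t test on change uses baseline HFIS only by subtraction and omits the randomisation strata: a valid test, but it can give up precision that a prespecified covariate model would recover

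*Protocol article*

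**What the plan says.** - **Outcome** (Outcome Measures): "The primary outcome assessed will be the changes in participant food insecurity score (evaluated by the HFIS) from baseline to 3 months".
- **Sizing** (Sample Size): an independent-samples t test of mean change in the two arms. On the effect the article says: "This results in a difference of –0.5 between the mean changes of the 2 groups". The planning inputs beside it are an SD of 1.5 for the change score, 80% power and a significance level of .05. The result is 141 per arm, 282 in total.
- **Randomisation** (Randomization, Allocation, and Blinding): "Randomization will be stratified according to gender and food insecurity level (low/moderate vs severe) with permuted blocks of six".
- **Between-arm analysis** (Data Analysis): independent-sample t "tests will be used to compare the intervention group and control group on the same outcomes". No covariate is attached to this test.
- **Regression models** (Data Analysis): these are introduced as a study of the association between each outcome and candidate covariables. A covariate enters if its univariate P value is below .25 or it is thought clinically relevant, and backward selection at .05 follows. Multilevel and sensitivity analyses are to be done when appropriate. Baseline HFIS, the strata and the treatment effect are not named.
- **Distribution of the score** (Sample Size): in the national survey, "about 80% of those in the low food insecurity level obtained just 1 point in the food insecurity score".

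**The concern.** A change score fixes the coefficient of the baseline value at 1. That is efficient only if the regression slope of the 3-month score on the baseline score is close to 1. There is reason to doubt this here: a participant who enters with 1 point can fall by at most 1 point, while higher scorers have more room to fall. The article reports no data on how strongly change depends on baseline, so this is plausible rather than shown.

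The strata are a second source of precision. Stratifying reduces the true variability of the difference between arms, but a t test that omits the strata estimates its standard error as if they had not been used. The food insecurity stratum also pools low and moderate scorers, so it does not balance the score within that group.

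At stake is the precision of the primary comparison. The trial is sized at almost exactly 80% power, and the Sample Size section states no allowance for loss to follow-up.

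**Working it through.** **Inputs from the article:** difference 0.5, SD of change 1.5, power 0.80, alpha .05, 1:1 allocation, 141 per arm. Two-sided testing is taken because only it reproduces the stated number (a one-sided test would need 112 per arm).

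**Assumed, because the article does not give them:** rho (correlation of baseline and 3-month HFIS), the ratio of the SDs at the two visits, the share of variance explained by the strata, and any loss to follow-up.

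**1. The plan's own figure.** n per arm = 2 × [1.5 × (1.960 + 0.842) / 0.5]² = 141.3. This rounds up to 142, and the exact noncentral t calculation gives 143. At 141 per arm, power is 0.799 (normal) or 0.797 (noncentral t). The stated 141 is consistent with the unadjusted t test.

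**2. Adjusting for baseline, equal SDs.** With common SD s at both visits, the variance of change is 2s²(1 − rho) and the residual variance after adjustment is s²(1 − rho²). The ratio is (1 + rho)/2, so the SD to use is 1.5 × √[(1 + rho)/2]. Power by noncentral t, 141 per arm:

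| rho (assumed) | variance ratio | SD | power |
|---|---|---|---|
| t test on change | 1 | 1.500 | 0.797 |
| 0.3 | 0.65 | 1.209 | 0.933 |
| 0.5 | 0.75 | 1.299 | 0.896 |
| 0.7 | 0.85 | 1.383 | 0.857 |
| 0.8 | 0.90 | 1.423 | 0.836 |
| 0.9 | 0.95 | 1.462 | 0.816 |

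**3. Unequal SDs.** If the 3-month SD is k times the baseline SD, the ratio becomes k²(1 − rho²) / (1 + k² − 2k·rho). With k = 1.2 (assumed), power is 0.848, 0.810 and 0.798 at rho 0.5, 0.7 and 0.8. At rho 0.8 the ratio is 1.44 × 0.36 / (2.44 − 1.92) = 0.997. The gain disappears because the slope, k × rho = 0.96, is almost 1. A 3-month SD below the baseline SD would enlarge the gain.

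**4. Loss to follow-up.** With an assumed 15% loss (141 × 0.85 = 119.85 per arm) and equal SDs, power is 0.729 for the t test and 0.843 or 0.796 after adjustment at rho 0.5 or 0.7.

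**5. Strata alone.** Suppose the strata explain a share R² of the variance of change. The unadjusted test then has true type I error 2 × [1 − Φ(1.96/√(1 − R²))]. Power below is by normal approximation, 141 per arm:

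| R² (assumed) | type I error, unadjusted | power, unadjusted | power, adjusted |
|---|---|---|---|
| 5% | 0.044 | 0.805 | 0.819 |
| 10% | 0.039 | 0.812 | 0.839 |
| 20% | 0.028 | 0.826 | 0.879 |

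These gains do not add to those in step 2, because the food insecurity stratum is itself a coarse form of the baseline score.

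**6. Chance imbalance.** With equal SDs, a baseline imbalance of one point shifts the difference in change by −(1 − rho): half a point at rho 0.5 and 0.3 of a point at rho 0.7.

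**The case against.** The strongest reply is that this is a choice of efficiency and not an error. The analysis matches the test used for sizing, the trial reaches its stated power without adjustment, and the test is valid. All of that stands. It limits the seriousness of the point but does not remove it: the article names the between-arm method, and that method leaves out factors on which the trial is stratified.

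A second reply is that the regression models in Data Analysis already allow for adjustment, and that exact covariates are usually left to an analysis plan. In part this is fair, since baseline HFIS, gender and stratum could enter as clinically relevant. But those models are presented as association analyses, they do not name these covariates or the treatment effect, and backward selection could remove any of them. They mitigate the problem and do not supply a prespecified adjusted treatment estimate.

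A third reply is that the size of the gain cannot be known from the article. This is correct. Entry requires food insecurity, so the baseline score is cut off from below while the 3-month score can reach zero. A larger SD at 3 months is therefore possible, and it would shrink the gain.

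A reader might also infer more than the article supports:
- *That baseline is ignored.* It is not, because the change score subtracts it. Only covariate adjustment is missing.
- *That baseline imbalance passes in full into the result.* It enters by a factor of about (1 − rho), and stratification limits imbalance between severe and non-severe participants.
- *That the test is biased or inflates the type I error.* Step 5 shows the opposite direction.

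**Conclusion.** The point holds as a matter of precision and of matching the analysis to the design. With equal SDs at both visits, the stated t test gives up about 2 points of power (rho 0.9) to 14 points (rho 0.3), and about 10 points at rho 0.5. The loss could be close to nil if rho is high and the 3-month SD exceeds the baseline SD. Since rho and the SD ratio are not in the article, only this range can be stated, and no single figure should be quoted as the loss. The conclusion that the test is valid and somewhat conservative does not depend on those assumptions. The change is worth making because it needs no new data and the sizing has no stated reserve, but the trial's conclusions would not be invalid without it.

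**What to change.** Prespecify as the primary analysis a linear model of 3-month HFIS on arm, with baseline HFIS, gender and food insecurity stratum as fixed covariates and no covariate selection. Report the adjusted difference between arms with its 95% confidence interval. Use the same model for each continuous secondary outcome, with that outcome's own baseline value in place of baseline HFIS. Keep the t test on change as a sensitivity analysis, and state that the stepwise regression models are exploratory and do not provide the treatment comparison.

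The cost is wording only. Baseline HFIS and gender are already collected, the stratum is known at randomisation, and the sample size stays at 282. The article describes recruitment as still to start, so the change can be fixed before any outcome data exist.

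### Skewed serological markers are to be compared by unadjusted t tests on change with no transformation stated: valid, but well short of the power that log-scale, baseline-adjusted ANCOVA would give

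*Protocol article*

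**What the plan says.** Under Outcome Measures, the protocol article places tumor necrosis factor and the following among the 3-month secondary outcomes: "changes in serological markers of cardiovascular risk (insulin resistance, cholesterol levels, hemoglobin A_1c_, high sensitivity C-reactive protein, adipocytokines, interleukin 1, interleukin 6". Each is therefore defined as a change from baseline.

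Under Data Analysis, the serological markers are in the list of outcomes for which two-tailed t "tests will be used to compare the amount of change within each group". For the comparison between arms, independent-sample t "tests will be used to compare the intervention group and control group on the same outcomes".

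The same section foresees nonnormality, but only for description: continuous variables are given as mean and SD, "or in case of nonnormal distribution as median and interquartile range". No transformation or baseline term is attached to the test itself.

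A later paragraph adds regression: "The association between each outcome and the candidate covariables will be performed using generalized models". Covariates enter on a univariate P value below .25 or on clinical relevance, and then face backward selection at .05. Neither the baseline value of the marker nor a log scale is named.

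**The concern.** Inflammatory markers and insulin resistance are usually right-skewed: most participants have low values and a few have very high ones. On the original scale, the variance of the change comes mainly from those few, so a shift in typical values is hard to see. A difference in change scores also uses the baseline less efficiently than adjusting for it.

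The plan thus allows a marker to be described by its median and then tested on its mean change. At stake is a missed effect: the blood-marker outcomes, for which every participant gives samples, could be read as null although typical values had moved.

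**Working it through.** **The plan's own figure.** The Sample Size section covers only the food insecurity score: difference 0.5, SD 1.5, power 0.80, α .05. Two-sided, n per arm = 2 × (1.96 + 0.84)² × 1.5² / 0.5² ≈ 141, as stated; the power at 141 per arm is 79.9%. No power is stated for any marker.

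**Inputs for the markers.** From the document: 141 per arm and 1:1 allocation. Assumed, because the document gives nothing: lognormal marker; SD of the log value s = 0.6 or 1.0; correlation ρ = 0.6 between baseline and 3 months on the log scale; every intervention participant's value multiplied by r (0.80 or 0.75).

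**Formulas (normal approximation).** Power = Φ(z − 1.96), where
- log-scale ANCOVA: z = |ln r| / [s √(1 − ρ²) √(2/141)]
- t test on log change: z = |ln r| / [s √(2(1 − ρ)) √(2/141)]
- t test on raw change: z = (1 − r) e^(s²/2) / √[(V_control + V_intervention)/141], with V_control = 2v − 2c, V_intervention = v(1 + r²) − 2rc, v = e^(s²)(e^(s²) − 1) and c = e^(s²)(e^(ρs²) − 1).

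**Strong skew: s = 1.0, r = 0.75.**
- Log ANCOVA: 0.288 / (0.800 × 0.119) = 3.02, power 86%.
- Log change: 0.288 / (0.894 × 0.119) = 2.70, power 77%.
- Raw change: v = 4.67, c = 2.23, V_control = 4.87, V_intervention = 3.95. The difference in means is 0.25 × 1.649 = 0.412 and its SE is √(8.82/141) = 0.250, so z = 1.65 and power is 38%.

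**Moderate skew: s = 0.6, r = 0.80.**
- Log ANCOVA: 0.223 / (0.480 × 0.119) = 3.90, power 97%.
- Log change: 0.223 / (0.537 × 0.119) = 3.49, power 94%.
- Raw change: v = 0.621, c = 0.346, V_control = 0.551, V_intervention = 0.466. The difference in means is 0.239 and its SE is √(1.017/141) = 0.085, so z = 2.82 and power is 81%.

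**Simulation of the same settings** (needed because the normal approximation is rough for skewed data):

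| Setting | Raw change | Log change | Raw ANCOVA | Log ANCOVA |
|---|---|---|---|---|
| s = 1.0, 25% fall | about 42% | 76–77% | about 60% | 85% |
| s = 0.6, 20% fall | about 80% | 93% | 93% | 97% |

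Separate runs put raw change at 39 to 42% in the first row and 80 to 82% in the second. Baseline adjustment and the log scale each contribute. Squaring the ratio of the z values gives (3.02/1.65)² ≈ 3.4 and (3.90/2.82)² ≈ 1.9: roughly how many times more participants the raw-change test would need.

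**Wider range.** With the effect set so that log ANCOVA has 79% power, and ρ from 0.5 to 0.85, raw change has 65 to 74% power at s = 0.2, 56 to 65% at s = 0.5, 43 to 51% at s = 0.8 and 28 to 31% at s = 1.2.

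**No effect.** Type I error of all the methods lay between 4.0% and 5.5% across runs.

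**Effect not proportional.** If values halve only in the top baseline quarter (s = 1.0, ρ = 0.6), power is about 32% for raw change, 42% for log ANCOVA and 51% for raw-scale ANCOVA.

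**The case against.** **Raw is inferred from silence.** The article names the t test and does not say that values stay untransformed; a t test on log values would fit its wording, and an unseen analysis plan might say so. This has some force, and the point is therefore put as no transformation stated. But the article fixes a test for these outcomes, defines them as changes, and raises nonnormality in the same section without carrying it to the test. A t test on change is also unadjusted for baseline on either scale.

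**The regression models may cover it.** The baseline value could enter as clinically relevant. It is not named, however, and backward selection could remove it. The models are also described as examining associations with covariates, not as the comparison between arms.

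**The effects are generous.** This stands. For a 10% fall at log-SD 1.0, power is about 10% for raw change and 19 to 20% for log ANCOVA, so a small effect would probably be missed by either method.

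**The log scale is not always best.** This also stands: when only high values fall, raw-scale ANCOVA does better. Both forms of ANCOVA still beat the t test on raw change.

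**A stronger reading.** A reader might infer that a few extreme values make the test invalid or produce false positives. The simulated type I error does not support that. Nor does the absence of a rule for values below the detection limit count against the article, since such detail is commonly left to the analysis plan.

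**Conclusion.** The point holds as one of efficiency. The planned test for the right-skewed markers is valid but leaves much of the available power unused: about 80% against 97% at log-SD 0.6 with a 20% fall, and about 42% against 85% at log-SD 1.0 with a 25% fall, at 141 per arm and correlation 0.6.

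The direction was the same at every log-SD and correlation tried. The size rests on assumed spread, correlation and effect, and the advantage of the log scale over raw-scale ANCOVA rests on a roughly proportional effect. For nearly symmetric markers (log-SD 0.2) the loss is about 5 to 14 percentage points; cholesterol and hemoglobin A1c probably lie near that end.

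These are secondary outcomes for which no power is claimed, so no stated figure is contradicted, and the primary outcome and the 141 per arm are untouched.

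**What to change.** In Data Analysis, replace the t test for the serological markers by an ANCOVA of the 3-month value on arm and the baseline value of the same marker. Fix the baseline term in advance and exempt it from stepwise selection.

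- For high-sensitivity C-reactive protein, interleukins, tumor necrosis factor, adipocytokines and insulin resistance, take logs of both values and report the ratio of geometric means with its 95% CI.
- For roughly symmetric markers such as cholesterol and hemoglobin A1c, keep the original scale and report the adjusted mean difference with its 95% CI.

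The scale for each marker should be named before unblinded data are seen. According to the Results section, recruitment had not begun when the article was written.

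The cost is a change of wording: no extra participants, visits or assays. The downside is that the skewed markers are reported as ratios of geometric means and not as differences in units, which is a different estimand, and that the log scale gains most when the effect is roughly proportional.

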A nutrition and physiotherapy assessment will be performed at baseline and end of intervention assessment (at 3 months). The nutritionist will collect data regarding food insecurity (Household Food Insecurity Scale [HFIS] adapted from the US Department of Agriculture Household Food Security Survey Module [21]), dietary habits (2-day 24-hour diet recall, Prevención con Dieta Mediterránea [PREDIMED] index [31], and food frequency questions), anthropometric data (height, weight, and waist circumference), body composition data obtained by bioimpedance (fat mass, fat-free mass, total body water), attitudes and barriers on diet, food expenses, and other resources for food. Regarding the dietary habits assessment, a second 24-hour diet recall will be performed by phone call interview performed within 1 week.

Physiotherapy assessment will be conducted aiming at collect data regarding physical activity (Elderly Mobility Scale [EMS] [32] and International Physical Activity Questionnaire [IPAQ]) and muscle strength (hand grip, knee extension, and hip flexion by using a dynamometer). The assessment scales used in the study are all Portuguese-validated versions, and the average time for the evaluation will be 90 minutes.

The nurse will perform a structured questionnaire in order to capture baseline knowledge on healthy lifestyles. This questionnaire will be repeated during the 3-month and 6-month follow-up assessments.

Blood samples will also be collected in order to obtain data regarding the nutritional status and serological biomarkers of cardiovascular risk (albumin and prealbumin levels, insulin resistance, cholesterol levels, hemoglobin A_1c_, adipocytokines, high sensitivity C-reactive protein, interleukin 1, interleukin 6, and tumor necrosis factor).

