At the 6-month follow-up time point, the assessment will be telephonically performed with the assistance of a CATI system (an in-house software platform) by a team of research assistants. These data will be collected in a standardized form; database access is protected by unique username and password for each research team member. In this telephone interview, we will collect data regarding food insecurity (HFIS [21]), dietary habits (2-day 24-hour diet recall, PREDIMED index [31], health-related quality of life and health status (E-5D-3L and FACIT-F), physical activity (IPAQ), consumption of health care resources (inpatient admissions and outpatient appointments), functional disability (HAQ), anxiety and depression symptoms (HADS), and lifestyle behaviors (see Multimedia Appendix 1 for a schedule of all collected data). Finally, the intervention group data regarding the adherence to the program will be monitored using the TV interactive data.

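### The unadjusted t test fixed for the primary HFIS comparison ignores baseline score and strata: it costs power, and it can bias the effect if 3-month loss depends on baseline differently by arm

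*Protocol article*

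**What the plan says.** Outcome Measures sets the endpoint: "The primary outcome assessed will be the changes in participant food insecurity score (evaluated by the HFIS) from baseline to 3 months". The Sample Size section bases the trial on an independent-samples t test of mean change: "This results in a difference of –0.5 between the mean changes of the 2 groups", with SD of change 1.5, power 0.80, α=.05 and 141 per arm. Data Analysis repeats that choice for the group comparison: independent-sample t "tests will be used to compare the intervention group and control group on the same outcomes". Neither section brings in baseline HFIS or the stratification factors, which the Randomization section gives as gender and food insecurity level (low/moderate vs severe).

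HFIS is taken in clinic at baseline and 3 months, and once more later: "At the 6-month follow-up time point, the assessment will be telephonically performed", with HFIS among the items collected on that call. A participant can therefore lack a 3-month score and still have baseline and 6-month scores.

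Two other sentences in Data Analysis bear on this. Regression models are planned for the association of each outcome with candidate covariables, chosen by univariate screening and backward selection. Also, "Multilevel analysis and sensitive analysis will be performed when appropriate". Neither is tied to HFIS or to the treatment contrast.

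**The concern.** Change from baseline is usually negatively related to the baseline value: high scorers tend to fall and low scorers to rise, whatever the arm. A t test on change leaves that predictable variation in the error term. It also takes no credit for the balance that stratifying on food insecurity level provides.

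The same relation creates a route to bias. Suppose the 3-month scores that go missing in the TV arm come mainly from high or low baseline scorers, and those in the control arm do not. The two groups compared then differ at baseline, and the t test reads part of that difference as treatment effect. The TV arm carries a 12-week programme and controls do not, so a different pattern of loss by arm is plausible. The sample size has no spare power to absorb any of this.

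**Working it through.** **1. The plan's own figure.** Inputs from Sample Size: difference 0.5, SD of change 1.5, power 0.80, α=.05 (taken as two-sided).

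n per arm = 2 × [1.5 × (1.960 + 0.842) / 0.5]² = 141.3.

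The stated 141 reproduces to within rounding, and power at 141 is 0.799 (normal) or 0.797 (t). The 50% adherence factor is used before randomisation (1128 × 0.5 × 0.5 = 282), so nothing is held back for later loss.

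**2. Precision with baseline adjustment.** Assume equal SD σ at each visit and correlation r. The SD of change is σ√(2(1−r)); with σ = 1.5 and r = 0.5 it is 1.5, as planned. The residual SD after adjusting for baseline is σ√(1−r²) = 1.5 × √0.75 = 1.299. Power = Φ(0.5 / [SD × √(2/n)] − 1.96).

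| Scores per arm | t test on change (SD 1.5) | Baseline-adjusted (SD 1.299) |
|---|---|---|
| 141 (complete) | 0.5/0.1786 = 2.799; power 0.80 | 0.5/0.1547 = 3.232; power 0.90 |
| 113 (20% random loss) | 0.5/0.1996 = 2.506; power 0.71 | 0.5/0.1728 = 2.893; power 0.82 |

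Simulation gives slightly lower values in places: about 89% adjusted with complete data, and 69 to 70% (t test) against 80 to 82% (adjusted) at 20% loss.

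**3. How far this depends on r.** Holding the SD of change at 1.5, the residual SD is 1.5 × √((1+r)/2).

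| r | Residual SD | Adjusted power, 141 per arm | Adjusted power, 113 per arm |
|---|---|---|---|
| 0.3 | 1.209 | 0.94 | 0.87 |
| 0.5 | 1.299 | 0.90 | 0.82 |
| 0.7 | 1.383 | 0.86 | 0.78 |
| 0.8 | 1.423 | 0.84 | 0.75 |

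The gain shrinks as r rises but remains positive throughout.

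**4. Bias.** With equal SDs, the expected change falls by (1−r) for each point of baseline. If loss shifts the mean baseline of those analysed by m points in one arm only, the t test is off by −(1−r) × m. At r = 0.5, a shift of 0.32 points gives 0.16. Simulated with 141 per arm, normal scores and no true effect:

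| 3-month loss, TV vs control | Dependence on baseline HFIS | t-test bias | t-test type I error |
|---|---|---|---|
| 25% vs 10% | none | 0.00 | about 5% |
| 20% vs 10% | log-odds 0.5 per SD, TV arm only | about 0.07 | about 7% |
| 25% vs 10% | log-odds 0.5 per SD, both arms | 0.05 | 5.6% |
| 25% vs 10% | log-odds 1 per SD, TV arm only | about 0.16 | 12 to 14% |

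The sign of the bias follows the direction of dependence. In the last row a true −0.5 is reported as about −0.34 or −0.66. Baseline-adjusted analysis of the 3-month scores alone gives about 0.00 under the null and −0.50 under the alternative, with type I error about 5%.

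**5. What the 6-month score adds.** Under 20% random loss, a three-visit model has about 83% power against about 82% for baseline adjustment alone. The 6-month score matters more when 3-month loss follows the later outcome. With nominal loss of 20% vs 10%, loss tied to 6-month change at log-odds 0.5 or 1.0 per SD, correlation 0.6 between the two changes and the 6-month score always held, a true −0.5 is estimated as −0.54 or −0.59 by complete cases. Using baseline and 6-month scores gives −0.50 or −0.51.

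**6. Where the model does not help.** If loss depends on the unseen 3-month score itself, one such scenario gave null bias of −0.16 for the t test and −0.23 for the three-visit model.

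**The case against.** The strongest reply is that missing-data rules and analysis sets commonly sit in a statistical analysis plan, which is not shown here. A reader might infer that the plan commits to analysing complete pairs and deleting everyone else. It does not say so: that follows only from applying the test without imputation, and a t test can be run on imputed data. Silence on missing data is therefore no part of this point. What stands is that the article does fix the test, and the test is unadjusted whatever is done about missing scores.

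A reader might also infer that unequal loss by itself biases the result, or that the main harm is discarding 6-month scores. Neither holds. Unequal random loss gave no bias, and baseline adjustment without any 6-month data removes the baseline-driven bias and gives nearly all the power gain.

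The size of the bias is also open to challenge. The documents give no attrition figure, and 0.16 needs strong dependence in one arm only; milder settings give 0.05 to 0.07. That is fair, and it is why the precision argument, which needs no loss at all, comes first.

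Finally, Data Analysis does mention regression and multilevel analysis. As worded, the first concerns covariate associations and the second has no stated outcome or trigger, so neither replaces the t test as the group comparison.

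**Conclusion.** The point holds as a worthwhile improvement, at medium confidence. It does not show that the trial's result will be wrong. The fixed primary comparison is valid with complete data and reaches its planned 80% power, but it gives up about 10 percentage points that data already collected would supply (r = 0.5; about 4 points at r = 0.8, 14 at r = 0.3). At 20% random loss it falls to about 70%, while an adjusted analysis stays at about 80 to 82%.

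The bias is conditional: about 0.07 to 0.16 points on a target of 0.5, and only if 3-month loss depends on baseline HFIS differently in the two arms. Every loss rate, correlation and strength of dependence is an assumption. The calculations treat HFIS as normal, although Sample Size indicates that many participants will score only 1 point, so the figures are approximate.

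**What to change.** In Data Analysis, make the primary HFIS comparison a baseline-adjusted model that includes the randomisation strata, for all randomised participants as allocated. The preferred form is one longitudinal model of baseline, 3-month and 6-month HFIS with a common baseline mean, visit, arm-by-visit and strata. Its 3-month contrast is primary and its 6-month contrast secondary. Keep the independent t test on change as supportive. Add one delta-adjusted sensitivity analysis for participants with no 3-month score.

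The cost is a few lines of text. No visits or measurements are added, and Stata, the named software, can fit the model. There are two drawbacks to state openly. The model assumes data missing at random and is no better than the t test if loss depends on the unseen 3-month score, hence the sensitivity analysis. It also combines telephone with clinic HFIS. If that mixing is a worry, baseline- and strata-adjusted analysis of the 3-month score alone keeps most of the benefit.
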